
### Human subject protections

2.6

Ethical approval for the study was received from Tallinn Medical Research Ethics Committee on 16 of June 2016 (Decision No. 1487).

#### Active consent

2.6.1

Study participants were informed and consent was acquired in the following way:1.An administration representative from each school filled out and signed an informed consent form to apply to take part in the study. By signing the form, the school assured that they understood the conditions for participation (criteria for inclusion and exclusion of schools are described in Section 2.2).2.All parents of the children studying in the 42 classes participating in the trial were notified about the study in September 2016 and had three weeks to decide for their children to be included in the study and take part in the intervention. Parents received mail from their child's teacher that included the information letter and consent form. The information letter introduced the PAX GBG, aims and randomization principles of the study and data collection methods (e.g., children completing Go/No-Go tasks, teachers and parents evaluating children). Confidentiality issues were addressed, and it was emphasized that taking part in the study was voluntary, data would be collected on children whose parents agreed to the process and parents could elect to quit participating in the study at any time. In addition, a link to a short video [37] describing the study was added.Parents had to choose if they agreed or not with taking part in the study. It was all-encompassing opt-in consent; consenting parents approved data collections from children, teachers and themselves all at once. Parents who agreed had to select whether they wanted to fill in questionnaires on paper or online. Parents could return a hard copy of the signed consent form to the school or send a digitally signed form to the NIHD via email. Parents also had the option of requesting a consent form in Russian.3.Each child's verbal consent is obtained before each time one completes the Go/No-Go task. Experimental procedures are explained to the child prior to the task and children are informed about their right to stop completing the task at any time. Only children whose parents agreed to take part in the study complete the Go/No-Go task.

#### Data management during the research

2.6.2

Each student whose parents conceded to participate was assigned a study code, which protects confidentiality and allows for linking the data collected at different time points. Parental questionnaires include the study code and do not contain any information which would permit distinguishing individuals.

Teachers' questionnaires include the study code as well as the name of the student. The student's name is added on the teacher's questionnaire so that the teachers would know about whom they are filling out the questionnaire (as they need to fill out one questionnaire per each student in their class). The teachers' questionnaires are inserted to the database only with the study code. Same teacher stays with the class from first until fourth (included) grade in Estonia; hence teacher change between data collection points is not likely.

Only the research team members can access locked data containing children's names together with their codes. All databases hold only non-identifiable data and are accessible exclusively to the research team. The data will be analyzed anonymously and results presented in generalized format.

### Intervention

2.7

As described earlier, the PAX GBG includes a classroom-based game and evidence-based kernels. Teachers implement the methodology daily within the regular school curriculum, using kernels during all lessons where possible and GBG every day starting from the training. All children from the intervention classes receive the intervention regardless of whether they participate in the study or not.

The PAX GBG begins with creating a shared class vision displayed in the classroom. For developing and maintaining a supportive classroom environment evidence-based kernels are utilized daily. For example PAX Quiet (a cue for attention), PAX Voices (a cue for expected voice levels), Timer (to improve focus and increase time engaged in learning), PAX Stix (to increase equality and participation), Granny's Wacky prizes (motivators to increase wanted behaviors), OK/Not OK desk cards (providing feedback to groups and individuals), and PAX Tootle notes (express appreciation, thanks and recognition of accomplishments).

Once the kernels are used regularly in the classroom, the GBG is introduced and played. To play the game, the class is divided into teams. Teams work cooperatively and if they do not exceed a specified criterion of previously defined inappropriate behaviors within the game period, they win a simple activity reward (selected from Granny's Wacky prizes). At the beginning, children play the game for brief periods, with game sessions lengthening over time [22].

Competing as groups allows rewarding positive rather than deviant behavior. The students that are grouped together influence and assist each other to win the game, leading to the internalization of norms for appropriate behaviors in school and other settings [38]. Group rewards are conditional on the behavior of a group's members and, as such, supports cooperative behavior in the classroom [39]. Potentially destructive aspects of between-group competition are managed by periodically shuffling the composition of the groups [39].

#### Implementation of the intervention in Estonia

2.7.1

PAX GBG was adapted to Estonian schools during the school year of 2014/15. In the previous two years, 41 classes participated in the program.

There are 22 active mentors (currently coaching teachers) in Estonia. The mentors all passed a three-day training conducted by the PAX GBG program developer, [name], as well as by PAX GBG lead international trainer, [name], and took part in continuing education training organized by the NIHD. The Estonian PAX GBG mentors conduct teacher trainings in Estonia, lasting three days altogether. Each training day was carried out separately (i.e., not in sequence). Compared with United States, where teachers normally take part of 1-day training and receive one additional booster session [24], the training period in Estonia was extended in 2015 to improve implementation fidelity.

The first training day for intervention schools' teachers was conducted at the end of October 2016 and focused on theoretical background of PAX GBG. How to increase a child's well-being, how to use kernels in classroom and the scientific background of the PAX GBG was discussed. Teachers also received PAX GBG materials (manual, posters, harmonica, desk cards, Tootle Note blanks, PAX Stix, timer, and Granny Wacky Prizes cards). The second training day was two weeks later in November 2016. Before that, teachers had to finish home assignment, which included familiarizing themselves with the teacher's manual, creating a shared vision with children and practicing kernels in their classroom. During the second day, the teachers shared their first experiences and learned the classroom-based game.

An additional one-day training took place in February 2017. Topics like assigning roles to students, playing the game without notifying the students and using PAX GBG outside the classroom were discussed. The third day of training was open for all practicing teachers to take part in regardless of which year they commenced administering PAX GBG in the classroom.

#### Implementation support system in Estonia

2.7.2

PAX GBG mentors support implementation of the intervention and regularly visit the classroom over a one-year period. Per each implementing teacher, the mentor spends approximately 30 h per school year on class visits that include coaching sessions. During the 2016/17 school year, mentors visit each class between 10 and 14 times. They also provide counseling via e-mail and phone. In the beginning, the visits occur every two to three weeks. When a teacher feels more confident, the visits are less frequent. During the second year (in this case, 2017/18), teachers can continue using the PAX GBG methods and participate in the third day of the training in the winter of 2018. They also receive up to two visits from the mentor at the beginning of the school year to encourage continuing with the intervention. There is no cut-off for the intervention and the implementation of the methodology is expected to become a daily practice for teachers, even as they do not receive regular support during second school-year from mentors.

One school visit normally lasts two to 3 h. During the visit, the mentor observes the classroom environment and the use of PAX GBG. After the observation, the mentor makes recommendations for the teacher. During each school visit, mentors fill out observation forms (implementation rubric and progress evaluation forms), which supplies mentors with input pertaining to the progress and implementation quality of the intervention in the classroom.

### Controls

2.8

The trial uses a waitlist control design and PAX GBG will be implemented in the control schools after the end of the trial, if schools are still interested to use PAX GBG by that time. As such, control schools carry out classroom work as usual.

To monitor what control schools deliver in the classrooms, teachers provide information about the methodology and programs they use to support children's wellbeing during baseline data collection.

### Objectives and outcome measures

2.9

The study's main objective is to evaluate whether PAX GBG affects children's overall mental health (primary outcome), as measured by the total difficulties score on the teacher-completed Strengths and Difficulties Questionnaire (SDQ) [40].

Secondary objectives are to examine whether intervention affects:-aspects of children's social and emotional well-being, as measured by the subscales of SDQ, completed by teachers and parents (see below for further details);-children's inhibitory control, as measured by the visual computerized Go/No-Go task completed by children;-children's symptoms of attention deficit hyperactivity disorder (ADHD), as measured by the parent-completed Swanson, Nolan, and Pelham – IV Questionnaire [41];-teacher's self-rated efficacy in classroom management, as measured by the teacher-completed Teachers' Sense of Efficacy Scale [42]; and-classroom's overall behavior, as measured by the teacher-completed four-item measure [43].

Additional data is also collected about intervention fidelity.

#### Primary outcome measure

2.9.1

The Estonian version of the SDQ with an impact supplement is employed to assess children's mental health [40]. SDQ is a brief behavioral screening questionnaire for assessing four-to 17-year olds, which has been applied internationally and demonstrated satisfactory validity and reliability across different populations [44]. The SDQ consists of 25 statements rated on a three-point Likert scale from (0) not true to (2) certainly true. It comprises five subscales - emotional symptoms, conduct problems, hyperactivity/inattention, peer relationship problems and prosocial behavior. Responses to the subscales, apart from the prosocial subscale, lead to a total difficulties score, which has been found to be a psychometrically sound measure of overall child mental health problems [45], [46]. Ratings of child distress and the impact of difficulties combine to form the impact supplement scale. In addition to using SDQ scores as continuous variables, scores will be classified to identify likely cases with mental health disorders. Due to the lack of normative data on this measure in Estonia, cutoff scores from the United Kingdom will be used instead [47].

Teacher SDQs (primary measure) are compared with a single-sided version (without the impact supplement) of the parent-rated SDQs [48]. Data triangulation is used to increase the credibility and validity of the results [49].

#### Secondary outcome measures

2.9.2

The *visual computerized Go/No-Go task* is used to assess children's inhibitory control. The PAX GBG seeks to improve children's self-regulation skills through rewarding inhibition of aggressive, disruptive, impulsive and inattentive behavior [7]. Response inhibition serves as a cognitive marker for the study of impulsivity, while its manifestation in childhood is associated with delinquency, antisocial behavior, ADHD and drug addiction [50]. Go/No-Go task has demonstrated to be the most sensitive neuropsychological measure of impulsivity that reflects changes in response inhibition in real time [51].

The Go/No-Go task was developed for the purposes of the present study specifically for children between the ages of seven and eight. The task was developed during the summer of 2016 by the Center for Cognitive Behavior Therapy (in collaboration with the private limited company, Science Programming Team) and piloted with 52 children between seven- and eight-years old. The task is set up with the Java program and the number of commission and omission errors together with reaction times for both go and no-go tasks are registered.

12 pairs (24 schools) were randomly selected by an independent statistician from ERSI to take part in the assessments. As conducting assessments at each school takes one to two days, and time for the data collection is limited (three weeks during each wave), half of the schools taking part in the study were randomly chosen to complete the Go/No-Go tasks.

The primary purpose in the Go/No-Go task is to inhibit prepotent responses. The stimuli - pictures of animals - are presented in the center of a laptop computer screen. Specifically, pictures are presented for 1000 ms with 1000 ms intervals on a 13.3 inch screen. There are three blocks in total, each block containing four series with three Go and one No-Go condition appearing in random sequence. 30% of stimuli are distractors (i.e., No-Go stimuli) and 70% targets (i.e., Go stimuli). Children are instructed to fixate on the cross in the middle of the screen and press the spacebar with their dominant hand as quickly and accurately as possible when the target stimulus is presented and to inhibit their response when a distractor stimulus appears. Reaction times are measured and the numbers of commission and omission errors are registered for each block. Reaction times reflect self-control associated to stimuli, commission errors problems in behavioral inhibition and omission errors attentional difficulties. The experimenter reads loudly the instructions featured on the computer screen before each series. The practice trial was added before the experiment to control that children understood the nature of the task. It takes between seven and 8 min per child to complete the practice trial and experiment.

The task is conducted individually in a quiet room at a child's school during regular school hours by master- or doctoral-level psychology students. All task conductors were instructed by the task developer and NIHD, written guidance on how to administer the task was also provided.

*The Swanson, Nolan, and Pelham – IV Questionnaire (SNAP-IV)* is utilized to measure the symptoms of ADHD among children. Each of the 18 items of the SNAP-IV assesses ADHD core symptoms of hyperactivity/impulsivity and inattention [41] and are rated by parents. Items are rated on a four-point scale from (0) not at all to (3) very much. The SNAP-IV questionnaire has acceptable reliability and it satisfactorily distinguishes children withdifferent levels of ADHD concerns [41]. There is no normative data collected from Estonia, hence the original parental cutoff scores originating from United States will be used [52]. The SNAP-IV was adapted to Estonian for the Estonian Children Personality Behavior and Health Study [53].

*The Teachers' Sense of Efficacy Scale (TSES)* is employed to gauge teacher's self-rated efficacy and has demonstrated to be reasonably valid and reliable measure [42]. A 24-item measure evaluates teachers' perceptions of their sense of effectiveness as teachers on three subscales - student engagement, instructional practice and classroom management. Responses are supplied on a nine-point scale for each item from (1) nothing to (9) a great deal. Mean scores are calculated for each scale with a higher score indicating a greater sense of efficacy. The cross-cultural adaptation of the instrument was conducted for NIHD in 2015 by The Center for Applied Social Sciences (CASS) at Tartu University.

A *teacher-rated four-item measure* is used to assess classroom behavior. The measure originates from the Organization for Economic Co-operation and Development (OECD) Teaching and Learning International Survey (TALIS) 2013 teacher's questionnaire and asks to indicate how strongly a teacher agrees or disagrees with statements regarding classroom behavior on a four-point scale from (1) not at all to (4) completely agree [43]. There is no information available about the measures' validity and reliability.

Socio-demographic data is additionally collected from parents, including child gender and age, parental gender and age, parental nationality and home language, family structure, number of children, count of household members, financial situation of the household, current employment status and parental education. Teachers provide information about their gender and age, years of experience teaching and whether and what methods they are using in the classroom to support children's mental health.

#### Data collection procedure

2.9.3

Table 1 describes the schedule of enrolment, intervention and assessments. Baseline information was collected at the beginning of the 1st academic year (3 weeks during September/October 2016), all participants were blind to allocation at this point. Post-tests will follow at the end of the 1st academic year (May 2017) and the 2nd academic year (May 2018).

**Table 1 tbl1:** Schedule of data collection.

Time point	Study period			
	Enrolment	Evaluation		
	Pre-baseline	Baseline (October 2016)	First post-test (May 2017)	Second post-test (May 2018)
**Enrolment**				
Eligibility screen	X			
Informed consent	X			
Matching	X			
**Interventions**				
PAX GBG, intervention group				
Usual practice, control group				
**Parent-rated Assessments**				
Sociodemographic variables		X	X	X
Child's mental health and prosocial skills (SDQ)		X	X	X
Child's symptoms of attention deficit hyperactivity disorder *(*SNAP-IV*)*		X	X	X
**Teacher-rated assessments**				
Background variables		X	X	X
Child's mental health and prosocial skills (SDQ)		X	X	X
Teacher's sense of efficacy (TSES)		X	X	X
Classroom behavior		X	X	X
**Child-completed assessments**				
Response inhibition (Go/No-Go task)		X	X	

During the 1st year the teachers from intervention classes receive training as well as regular mentoring hence the first post-test demonstrates the effects following active implementation. Previous trials have showed that the immediate effect of GBG will be measurable by the end of 1st year, while follow-ups have found continuing positive effects of the intervention even if the intervention is not implemented after first year [54]. There is no cut-off for intervention during the study period, but as the teachers do not receive regular implementation support during 2nd academic year, the implementation of the intervention may decline during that time. The rationale for second post-test is to find out if the intervention has long-term effects, which will be measurable regardless if teacher's use or don't use the intervention.

First post-test is given priority in determining the intervention effects. The control group will not receive the intervention until the second post-testing in May 2018 has been completed.

Teacher's fill out SDQs for each child taking part in the study and the teacher's questionnaire (containing teacher's background information, TSES and the classroom behavior measure) during all three assessments. Paper versions of the questionnaires are sent to schools by NIHD.

Parents fill out electronic or paper versions (according to their preference) of parental questionnaires (containing sociodemographic, SDQ and SNAP-IV data) also three times. Electronic parental questionnaires are sent to parents via email. Paper versions are sent through schools and parents return filled out questionnaires to the NIHD in prepaid envelopes.

Subgroups of children complete computerized Go/No-Go tasks twice - in October 2016 and May 2017.

#### Assessment of implementation

2.9.4

Intervention fidelity and children's exposure to the intervention are measured via (1) structured observations and (2) teachers' self-reporting.1)Intervention adherence is evaluated via observations. Observations are carried out by mentors and by independent researchers during the 2016/17 school year.a)All independent researchers have passed the PAX GBG teacher's training and 2-h instruction. They visit one lesson per class during spring semester (February 2017) in first year. Researchers' data collection point was set for mid-term to assess intervention adherence after training is completed and teachers should be able to implement intervention correctly. All researchers conduct the first observation in pairs with a senior member of the research team to ensure the inter-rater reliability. Observers stay in the classroom for one lesson and ask the teachers to play a five-to 15-min PAX GBG game. They fill out the PAX GBG implementation rubric.b)Data collected from independent researchers will supplement information collected from mentors, who visit and observe classrooms regularly during the 1st academic year. As mentors are supporting the delivery of the intervention, additional data collected from independent researchers strengthens the research credibility. Mentors fill out two scoring rubrics (adapted from the PAX GBG implementation rubric and PAX GBG progress evaluation form) during each visit to the class.*PAX implementation rubric* contains 32 statements divided to seven dimensions: preparing students for the game (6 items), using the timer (3 items), team structure (4 items), recording student behavior (4 items), responding neutrally to misbehavior (4 items), game review after the game (4 items) and rewarding the students (7 items). Observers mark ‘no’ (0) or ‘yes’ (1) answers when the teacher used or did not use the method. Open-field text boxes are included to allow observers to record reasons for their ratings. If a teacher is using the methods correctly and scoring more ‘yes’ answers than ‘no’, then the intervention is implemented with higher fidelity.The *PAX progress evaluation form* helps mentors evaluate the overall development and use of the PAX GBG methods within the classroom. It features six dimensions: usage of the PAX GBG vision, vocabulary, cues, Tootle notes, additional kernels and a teacher's general attitude and openness towards the PAX GBG. In the beginning, a mentor has to give responses to statements about whether the teacher is using the method (‘true’ or ‘false’ answers) for each dimension. The next statements focus on the use of practices, for which the mentor has to choose between answers on a three-point scale (2 = ‘certainly true’, 1 = ’somewhat true or 0 = ‘not true’).2)Children's exposure to the intervention is measured via teachers' self-reporting. Teachers use a web-based recording system to submit the number of games they have played during each week and the duration of each game played. This data is summed up across the school year and calculated into total number of games implemented and total number of minutes for which the PAX GBG was implemented.

### Statistical analysis plan

2.10

Demographic and baseline characteristics at the pupil level will be summarized using means and standard deviations (or medians and inter-quartile ranges) for continuous variables and percentages for categorical characteristics.

For analyzing the intervention effects on child outcomes, two scenarios are presented. First one will be used when matching has been effective (correlation between paired cluster response means (SDQ total difficulties) at baseline is at least moderate i.e. above 0.4) and takes into account the matched-pair design. Multilevel linear models with three levels (child, school, and pair) will be used with continuous responses (i.e. SDQ total difficulties mean score at post-test), where intervention group (PAX GBG vs. control) will be entered at the school level as a fixed effect, random effects will model differences between pairs and variation of the intervention effect among pairs. Covariates (i.e. gender and pre-intervention score) will be included at child-level. Binary outcomes (i.e. SDQ bandings no risk/at risk) will be compared between trial arms using multilevel generalized linear models. Even though pair-matched cluster randomized trials have analytical limitations, the focus of analysis will be on the overall effect of intervention, which can still be estimated [55].

Second scenario will be used when matching has been ineffective (i.e. correlation is small). As suggested by research [56], [57], breaking pair matches and treating the design as completely randomized might be useful strategy. Two-level hierarchical linear models (child, school) will be used with continuous responses and Generalized Estimating Equations (GEE) with the ‘sandwich estimator’ for robustness for binary responses. This approach will help to find out if and how many children will transit from ‘at risk’ to ‘no risk’ banding.

Multilevel models will use maximum likelihood estimation to handle missing data, assuming that data is missing at random [58]. GEE requires stronger assumption of missing data mechanism and assumes data is missing completely at random.

Secondary analysis will seek to find out whether the intervention has effect on child's inhibitory control and on symptoms of ADHD. Differences from baseline to post-assessment between the two trial arms will be estimated using multilevel models, including child-level covariates (i.e. baseline response inhibition/baseline ADHD score and gender). Analyzing the intervention effects on teachers will be conducted with same scenario as the effects on children. Two level models will be used to take into account the pair-matched randomization and linear regression when matching has not been effective. Teacher's gender, age and years of experience teaching will be added as teacher-level covariates.

Explanatory analysis will be conducted to examine potential moderators of intervention effects. The aim is to find out if the intervention has different effect to children based on their baseline risk-status (i.e. no risk vs. at risk on SDQ) and socio-demographic factors (i.e. family structure and socioeconomic status), using four-level (with pair-matched design) or three-level (when matching was ineffective) models with repeated measures entered as first level variables. Secondary analysis about the effects to child's inhibitory control and to teacher's self-efficacy as well as explanatory analyses are purely exploratory, with any significant findings needing to be replicated in other studies as the power of these analyses is low.

Intervention fidelity will be reported descriptively.

Analysis will be made without multiplicity adjustments as the main purpose is to compare intervention and control group using a single primary variable. Secondary objectives are adding to the value of the intervention and supporting the hypothesis relating to the primary variable (positive effect on children's mental health).

Impacts are estimated on the basis of modified intention to treat (mITT) [59], excluding randomized schools deemed ineligible immediately after randomization. Even though this type of estimation can introduce bias [60], it is believed that excluding two randomized schools as well as their matched participants from the analysis is sensible. Thus, data is collected from 42 schools and analysis will be based on their input.

Trial reporting will follow the CONSORT guidelines [61].

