### Minimum detectable effect size

2.5

A calculation was carried out to estimate the effect size the trial could detect as statistically significant. Cohen's d was used as an effect size measure. As an outcome variable, the *Teacher-Rated Strengths and Difficulties Questionnaire* (SDQ) total difficulties score at first post-assessment was considered.

For calculating the minimum detectable effect size (MDES) we considered two scenarios. For the first, we took into account the matched-pair design. However, as our matching criteria had presumably only weak associations with the outcome variable, the MDES calculations were also performed using simple cluster random assignment. In both cases, we used a significance level of 0.05 and a power value 0.8; average class size was an estimated 20 children. For the first scenario an intra-cluster correlation coefficient (ICC) of 0.15 was assumed for children in the same pair of schools. The effects of the pairs of schools were treated as random - with random intercepts and random effects on intervention. To account for intervention effect heterogeneity values of 0.5 and 0.75 were employed as a ratio of the variance of the intervention effect between pairs to the variance between pairs. On these conditions, 21 pairs with one intervention and one control school resulted in a MDES of 0.257 (or 0.286 if the random effects variance ratio was 0.75). Adding covariates to the children level (i.e. gender and baseline score) with an assumption of 20% variance reduction decreased the MDES value to 0.243 or 0.273.

With the second scenario, we discarded the level of pairs and assumed an ICC of 0.15 for children in the same school. The ICC for the primary outcome measure was based on earlier research in the field [32], [33]. The effects of the schools were considered as random intercepts. With 42 schools randomized to the intervention or control groups on a 1:1 bases, this scenario resulted in a MDES equal to 0.389. Again, adding children-level covariates (assuming a 20% variance reduction) diminished the MDES, yielding 0.380.

In other school-based intervention trials, the effects on students' mental health and well-being were found to vary between small and moderate [34]. Previous trials of GBG have found the effects on students behavior also to vary between small and moderate [35], [36]. Based on the calculations, we are aware that statistical power is an issue with this trial and we might be able to detect moderate effects.

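### Section 2.10 fixes maximum likelihood where REML with small-sample degrees of freedom would hold 5%: the primary test runs at about 5.5-5.6% with a t reference, and at 6-7% only if Wald z tests are used

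*Protocol article*

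**What the plan says.** Section 2.10 (Statistical analysis plan) analyses continuous child outcomes, including the primary teacher-rated SDQ total difficulties score, with multilevel linear models. There are three levels (child, school, pair) if matching proves effective, and two (child, school) if it does not. Intervention group enters at school level. On estimation the article says: "Multilevel models will use maximum likelihood estimation to handle missing data", under a missing-at-random assumption. It names no degrees-of-freedom method and no z, t or likelihood-ratio reference.

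Binary outcomes differ by scenario. With effective matching they "will be compared between trial arms using multilevel generalized linear models". With ineffective matching they use "Generalized Estimating Equations (GEE) with the ‘sandwich estimator’ for robustness for binary responses". The text does not say whether the sandwich is corrected for a small number of clusters.

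Section 2.5 (Minimum detectable effect size) states "we used a significance level of 0.05 and a power value 0.8", with 42 schools or 21 pairs. Section 2.9.2 gives the size of the Go/No-Go subset: "12 pairs (24 schools) were randomly selected by an independent statistician". Section 2.10 treats the inhibitory-control analysis as exploratory and applies no multiplicity adjustment, because inference rests on a single primary variable.

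**The concern.** The precision of the intervention effect depends on the number of schools or pairs, not the number of children. With so few units, two things can push a nominal 5% test above its level. One is a between-cluster variance estimate that ignores the fixed effects fitted at that level. The other is a normal reference where a t reference is needed. Full ML brings in the first. Whether the second also applies is left open.

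The reason given for ML is missing data. REML is also likelihood-based, uses the same observed data and rests on the same missing-at-random assumption, so nothing is gained on that score by preferring ML. Kenward-Roger, the usual small-sample remedy, is built on REML.

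The trial's error control rests on the one primary test, and section 2.5 concedes that power is limited. A borderline primary result is therefore plausible, and there an interval that is slightly too narrow can change the conclusion.

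**Working it through.** **Inputs.** From section 2.5: 42 schools or 21 pairs, 20 children per class, ICC 0.15, ratio of intervention-effect variance to between-pair variance 0.5 or 0.75, 20% variance reduction (R²) with covariates, alpha 0.05, power 0.80. Sidedness is not stated; two-sided reproduces the figures. From section 2.9.2: 12 pairs (24 schools) for Go/No-Go.

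**Step 1: reproduce the plan's own figures.**

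- 42 schools: MDES = [t(.975, 40) + t(.80, 40)] × √{4[0.15 + 0.85(1 − R²)/20]/42}. With R² = 0 this is (2.021 + 0.851) × √0.018333 = 2.872 × 0.1354 = 0.389. With R² = 0.2 it is 0.380.
- 21 pairs: MDES = [t(.975, 20) + t(.80, 20)] × √{[ratio × 0.15 + 2 × 0.85(1 − R²)/20]/21}. With ratio 0.5 and R² = 0 this is (2.086 + 0.860) × √0.007619 = 2.946 × 0.08729 = 0.257. The other three are 0.286 (ratio 0.75), 0.243 and 0.273 (with covariates).

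All six stated values are matched. Normal quantiles do not match: they give 0.379 in place of 0.389, and 0.245 in place of 0.257. The planning used cluster-level degrees of freedom.

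**Step 2: size of the ML standard error.** In the balanced case ML divides the between-unit sum of squares by the number of units J, where df is needed. The ratio of the ML standard error to the correct one is √(df/J):

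- 42 schools: √(40/42) = 0.976
- 21 pairs: √(20/21) = 0.976
- 24 schools: √(22/24) = 0.957
- 12 pairs: √(11/12) = 0.957

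**Step 3: type I error under each reference.**

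- ML with z: 2·P(t_df > 1.96·√(df/J))
- ML with t: 2·P(t_df > t(.975, df)·√(df/J))
- ML with likelihood ratio: reject when J·ln(1 + t²/df) > 3.841
- REML with z: 2·P(t_df > 1.96)

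| Units | df | ML, t | ML, LR test | ML, z | REML, z |
|---|---|---|---|---|---|
| 42 schools | 40 | 5.6% | 5.7% | 6.3% | 5.7% |
| 21 pairs | 20 | 5.5% | 5.9% | 7.0% | 6.4% |
| 24 schools (Go/No-Go) | 22 | 6.0% | 6.4% | 7.4% | 6.3% |
| 12 pairs (Go/No-Go) | 11 | 5.9% | 6.6% | 8.7% | 7.6% |

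**Step 4: simulation under the null.**

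- Two-level fits with gender and baseline covariates (6,000 replicates, ICC 0.15, 14 or 20 children per school), 42 schools: ML with z 6.3%, REML with t 4.8-5.0%. For 24 schools: 7.1-7.4% and 5.1-5.2%.
- Pair model (400,000 replicates, intervention-effect variance assumed from 0.075 to 0.30), 21 pairs: ML with z 6.5-7.1%, ML with t 5.1-5.6%, REML with t 4.7-5.0%. For 12 pairs: 7.2-8.8%, 4.5-5.9% and 4.0-5.1%. The low ends arise when the estimated effect variance is cut off at zero.

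**Step 5: GEE, scenario 2 binary outcomes only.** The article gives no at-risk rate, so rates of 10% and 20% and ICCs of 0.05 and 0.15 are assumed, with 42 schools of 16 children, an independence working correlation and 2,500 replicates. Rejection rates were:

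- plain sandwich with z: 6.2-7.9%
- plain sandwich with t: 5.5-6.7%
- Mancl-DeRouen correction with t on 40 df: 4.4-5.6%

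Simulation error is 0.4 to 0.5 points.

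**The case against.** The strongest reply is that the article states no z test. A reader might infer that the primary analysis runs at 6-7% because ML standard errors are too small. The document does not support that. Those rates need a Wald z reference, and half or more of the excess comes from that reference: REML with z would still give 5.7% (42 schools) or 6.4% (21 pairs). This part of the reply stands, and the higher rates are therefore stated only as conditional.

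A reader might also infer that planning and analysis contradict each other. They do not. Section 2.5 used t quantiles and section 2.10 is silent on the reference. If anything, the planning makes a t reference more plausible.

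Likewise, that the sandwich is uncorrected is an inference from silence, and a condensed article may leave such detail to a fuller plan. GEE never applies to the continuous primary score or to the paired analysis. The Go/No-Go analysis is already declared exploratory, so its higher rate threatens no confirmatory claim. All of this stands.

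Finally, the ML sentence could be read as meaning likelihood-based estimation in general, REML included. That is possible. But the text names maximum likelihood, and a later plan that uses REML would depart from its literal wording. This is a method the article fixes, not a detail it leaves out.

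**Conclusion.** The point holds at modest size. Read literally, section 2.10 fixes full ML for the primary analysis, which understates the standard error of the intervention effect by about 2.4%. In the balanced closed form the nominal 5% test runs at about 5.5-5.6% with t and 5.7-5.9% with a likelihood-ratio test. It reaches 6.3% (42 schools) or about 7% (21 pairs) only if Wald z is used. For the exploratory Go/No-Go subset the figures are about 6% with t and 7-9% with z. In the pair model with small effect variance, the t figures can be closer to 5% or below it.

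These figures assume near-equal class sizes and normal school effects. The GEE range of about 6-8% rests in addition on assumed at-risk rates and ICCs, and on an uncorrected sandwich with z, which the article does not state.

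**What to change.** For the continuous multilevel models, replace ML with REML and Kenward-Roger or Satterthwaite degrees of freedom, and name the t reference. The missing-at-random assumption is unchanged. REML with t gave 4.8-5.0% for 42 schools and 4.7-5.0% for 21 pairs.

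For scenario 2 binary outcomes, if GEE is kept, specify a small-sample bias-corrected sandwich (Mancl-DeRouen or Kauermann-Carroll) with t on about 40 degrees of freedom.

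The cost is a software option and slightly wider confidence intervals. If t was intended all along, they widen by about 2.5% (1/0.976 = 1.025). If z was intended, they widen by about 6% with 42 schools (2.021/1.960 × 1.025 = 1.057) or 9% with 21 pairs (2.086/1.960 × 1.025 = 1.091).
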